### Ethics approval and consent to participate

This study is approved by the Social Ethics Committee, on behalf of Wageningen University and Research. Potential participants are asked to participate in the research via a contact person in the participating organizations. They communicate their decision to the contact person, so consent to participate will be given orally. Before each interview and MCD session, participants will be asked to give written informed consent to record the interviews and MCD sessions. The information will be presented in a level of literacy that is considered acceptable for all employees (B1 literacy level). For observations, there will be an oral informed consent, given by the person in charge of the situation that is being observed. If anyone objects against observations, the researchers will not perform the observation. Both informed consent forms state that data from interviews, MCD sessions and observations will only be accessible for two researchers in this project ([name], [name]).

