Following on this is the second possible underlying cause for small effects in general, which is the lack of awareness about the ethical side of WHP. Employees can experience WHP interventions as interference in their privacy, which in its turn can a play role in employees’ decision whether to or not to participate [20]. On the other hand, as employees depend on their employer to maintain their job, employees might feel coerced to participate in WHP interventions [16]. Also, questions such as how far an employer can go in promoting employees’ health often rises [20] as well as whether (and to what extent) employees are responsible for their health or whether their employer is [19]. To conclude, it is important to take into account the ethical questions and the conflicting values that come along with WHP, as they can influence participation in WHP and the relationships at the workplace.

A third possible reason for low effectiveness in general is that employees generally lack voice in WHP [19]. This is considered of particular importance for lower SEP employees because, although there is ample knowledge about the health issues that lower SEP employees generally face (e.g. unhealthier lifestyle or poorer working conditions), insight is scarce in how these people experience their work and health promotion interventions, and how to target their health effectively considering their lifeworld [13]. The possible influence of lifeworld, as conceptualized by Habermas [21], on WHP can be found in a qualitative study among low SEP individuals [22]. These individuals indicated they were aware of the negative consequences of certain health behaviours, yet changing these behaviours had no priority due to other problems in their lives for which they indicated to ‘need’ certain types of unhealthy behaviours. Similar patterns may be seen in WHP: lower SEP employees may find health and health promotion important, yet the specific work setting they are in as well as their personal situation may make them feel powerless or not interested to improve their health.

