#### Recruitment

The aim is to include a maximum variety of stakeholders in the dialogues in order to capture a broad range of experiences and perspectives. Stakeholders will be contacted by means of a contact person in the participating organisations or directly and selected based on their willingness to participate.

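### Employees tell a contact person inside their own organisation whether they take part, with no stated protection for a refusal, although the protocol itself warns of dependency and coercion

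*Protocol article*

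**What the plan says.** The section on ethics approval and consent sets the route in two steps. On the invitation: "Potential participants are asked to participate in the research via a contact person in the participating organizations". On the reply: "They communicate their decision to the contact person, so consent to participate will be given orally". Written consent is then sought before every interview and dialogue session, but it is described as consent to recording. For observations, oral consent is "given by the person in charge of the situation that is being observed". The section adds that an objection by anyone stops the observation. Access to data from interviews, sessions and observations is limited to two researchers.

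The Recruitment section describes the route differently: "Stakeholders will be contacted by means of a contact person in the participating organisations or directly and selected based on their willingness to participate". 

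The Background lists, among the ethical difficulties of worksite health promotion, that "as employees depend on their employer to maintain their job, employees might feel coerced to participate in WHP interventions". The Discussion comes back to employees' dependency on the employer and to their weak voice in such programmes. The section on prerequisites for participation expects that some employees will not readily join a conversation about health.

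**The concern.** The protocol identifies a hazard and then adopts a procedure that is exposed to it. If an employee's job depends on the organisation, a yes or no given to somebody inside that organisation is not a neutral act. Some may agree because a refusal would be noticed. Others may stay away because they do not want to discuss health through a workplace intermediary. One of the two sites is a sheltered workplace for employees with disabilities, where dependency may plausibly be stronger.

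Two things are at stake. The first is voluntariness, which matters whatever the analysis. The second is whose views enter the evaluation. Stakeholders consulted at baseline say which changes count as relevant, those changes guide the choice of HRM indicators, and the changes that stakeholders perceive become the outcomes of the Social Return on Investment analysis. The design is justified by its attention to people who are usually not heard, so a reply route that may lose reluctant employees works against its purpose.

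**Working it through.** No arithmetic applies. The plan gives no sample size, power or participation figure on this point, so the check is a comparison of sections.

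1. **Who receives the decision?** The ethics section names one recipient, the contact person in the organisation. It gives no alternative for the reply.

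2. **Is that person independent of management?** The document gives neither a role nor a reporting line. It establishes only that the person is inside the organisation.

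3. **Does the Recruitment section change the answer?** It allows contact through the contact person or directly. That concerns how people are approached. It does not say to whom they reply, so the reply rule in the ethics section stands. The two sections still differ on the approach itself, because the ethics section mentions only the contact person.

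4. **Do the stated safeguards protect a refusal?**

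| Safeguard | What it covers | Does it shield a refusal to take part? |
|---|---|---|
| Written consent before each interview and session | Recording | No. It gives a further chance to decline, but the contact person already has the decision |
| Access limited to two researchers | Data from interviews, sessions and observations | No. Who accepted or declined is not listed |
| Any objection stops an observation | Observations | It gives a real veto, but no private way to use it is described |

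5. **Does the protocol regard the hazard as real?** Yes. Dependency and possible coercion appear in the Background, dependency appears again in the Discussion, and reluctance is expected in the section on prerequisites.

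6. **How far does the effect reach?** Consulted stakeholders influence the definition of relevant changes, hence the HRM indicators chosen, and the Social Return on Investment outcomes. The HRM analysis itself takes the perspective of all employees, and the Budget Impact Analysis uses whatever cost data the organisation holds. The document does not limit either data source to volunteers. The reach is therefore into what is measured and into the qualitative and social-value findings, not into every number.

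7. **How much of the exposure can be removed?** Dialogue sessions hold six to twelve people and may include management, so attendance is visible at work. A direct reply to the researchers can shield refusals and interview participation, but not session attendance.

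**The case against.** The strongest reply is that the protocol takes voluntariness seriously. Written consent is asked again before each interview and session, any individual can stop an observation, raw data stay with two researchers, direct contact is possible, and lower-SEP employees are the starting point for who joins the dialogue. The article also condenses a fuller document, which might describe how replies are handled. Much of this is fair. These provisions narrow the problem, but none covers the knowledge of who said no. The reply route is also a stated rule and not an omitted detail, so a fuller document would have to change it, not merely add to it.

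A reader might go further in four ways that the document does not support.

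- **The contact person acts for the employer.** No role is given. The concern needs only that the person is inside the organisation.
- **Selection on willingness contradicts the maximum-variety aim.** The aim is "The aim is to include a maximum variety of stakeholders in the dialogues in order to capture a broad range of experiences and perspectives" and the only criterion given is willingness. Willingness is a condition of any voluntary study and does not exclude variety. Further sampling criteria are the kind of detail that an article leaves to the full protocol.
- **An employee must object to an observation openly.** The document does not say how objections are made. It says only that they are honoured.
- **All outcomes are biased in favour of the intervention.** HRM and cost data are not restricted to volunteers. Pressure to join and loss of reluctant employees need not push the same way.

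**Conclusion.** The point holds as an unaddressed tension between a stated procedure and a stated concern, together with a mismatch between the Recruitment and ethics sections on how people are contacted. It should be corrected because it touches voluntariness and the credibility of findings meant to give employees a voice.

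Its size and direction cannot be derived. That would need participation rates and the difference in views between those who join and those who decline, and the document gives neither. The interviews and sessions undergo thematic analysis, so no estimated mean could be shifted by a calculable amount, and the authors state that they do not aim to evaluate causality. The conclusion assumes that a reply given to an insider may be known, or be thought to be known, within the organisation. The article says nothing that rules this out.

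**What to change.** Rewrite the recruitment and consent paragraphs so that they agree, as follows.

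- The contact person only distributes invitations.
- Employees reply directly to the researchers.
- The organisation is not told who declined.
- Before an observation, the people to be observed can raise the objection that the protocol already allows privately with the researcher.
- The Recruitment and ethics sections describe the same contact and reply route.

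The cost is slightly more researcher time for handling replies and scheduling, and a short ethics amendment. No additional participants are needed. The paragraph should also say plainly that attendance at group sessions remains visible to colleagues, so that the protection offered is not overstated.

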## Discussion

This paper describes the study protocol of the development and evaluation of moral case deliberation (MCD) as a worksite health promotion (WHP) intervention. MCD was chosen as a form of stakeholder dialogue because it pays attention to the multiplicity of values and interests in WHP and moral dilemmas at stake, employees’ lived experiences and power asymmetries in the work context. Responsive Evaluation was proposed as the type of evaluation of this study. This study will add to the current body of literature of WHP, as it provides a novel intervention as well as an original type of evaluation in the field of WHP.

The strength of this study is that Responsive Evaluation allows to respond to the dynamic and ambiguous context of the work setting. Organisations are constantly changing due to internal and external developments, which also changes the context in which WHP interventions are being performed. In order to maintain appropriateness of the intervention in a changed situation, Responsive Evaluation as well as the intervention offer the flexibility to adapt research goals and activities during the research process [24]. Ambiguity in the work setting is a result of power relations such as the dependency relationship between employer and employee. These power relations are also reflected in WHP, where the employer is in charge and the employee has little or no voice in WHP. The starting point of Responsive Evaluation is a bases of equality among various stakeholders [24, 34], as well as special attention to silenced voices such as employees in WHP, which makes this type of evaluation very suitable for the work setting.

To date, Responsive Evaluation is considered innovative in the field of WHP, where a Randomized Controlled Trial (RCT) is the gold standard. A RCT aims to evaluate causality by randomizing participants in an intervention and control group, and correcting for bias in the analysis [35]. One important difference between both types of evaluation is that Responsive Evaluation does not aim to evaluate causality. Instead, Responsive Evaluation aims to support the stakeholders in the setting under study to better understand their context themselves, which allows and supports them to make relevant practice improvements.

Responsive Evaluation results in context-specific outcomes. In the field of social sciences and health promotion, there have been discussions about the external validity of such context-specific outcomes [34, 36, 37]. In her commentary, Carminati (2018) [37] proposes transferability as an alternative term for generalizability for research that comprises only or mainly context bound data instead of quantitative data. Transferability means that outcomes of a study can be ‘transferred’ to other contexts by the readers through extrapolation and application of the ‘thick description’ of the findings [24, 37]. In this project, findings will provide organisations and researchers knowledge about how MCD was adapted to two different work settings, and what changes MCD led to in those settings. To ensure quality of transferability in this study several measures will be taken [38], such as discussing findings’ resonance with existing literature from different settings.

In the present study, health inequalities associated with socioeconomic position (SEP) are the starting point of this study. We acknowledge that intersectionality between SEP and other social categories such as gender, age, ethnicity, disability and first language, also influence chances on good health and thus health inequalities, due to various factors [39, 40]. The intersection between social categories should eventually be the starting point of interventions that aim to reduce health inequalities. Although the intervention and evaluation method of this study allows to adapt to the context of an organisation, including its population, it can be questioned whether diversity in all its facets is optimally taken into account, as the main focus is on SEP.

Additionally, WHP interventions alone cannot reduce SEP related health inequalities, as only half of the low SEP population is working [7]. This means that the other half does not have a job and therefore cannot be reached through the work setting. Moreover, these low SEP individuals do not profit from the positive effects of work on health and general well-being [41]. Therefore, these non-employed low SEP individuals presumably deal with poorer health conditions than employed lower SEP employees. Therefore, it is highly recommended to develop health promotion interventions, which may include dialogue methods as well, for non-employed low SEP individuals through other settings.

This protocol describes the development and evaluation of a worksite health promotion intervention consisting of moral case deliberation. The findings of this study may contribute to the body of literature about worksite health promotion and health inequalities, by evaluating moral case deliberation in two different work settings. Also, this study will provide novel insights into the suitability of Responsive Evaluation in worksite health promotion as an alternative to RCT. The results of this study are expected to be available in 2021–2022.

## Data Availability

Not applicable.

## Abbreviations

MCD: Moral case deliberation
RCT: Randomized controlled trial
SEP: Socio-economic position
WHP: Worksite health promotion
